### Data collection method

At this stage, by referring to premarital counseling centers and health centers, the samples with the Inclusion criteria are selected for the available sampling method. Before the implementation of the program, written informed consent will be obtained from the samples, and then the allocation of the samples into two control and intervention groups will be done by randomization.

### Sample size

The sample size was calculated according to (α = 0.05, β = 0.1, SD1 = 8.5, and SD2 = 19.8), 37 people in each group; However, due to increasing the validity of the study and considering at least 20% dropout, the number of samples will be 110 people (55 people in the intervention group and 55 people in the control group).

### Methods

The program designed in the previous phase will be implemented for young adult women about to get married in the intervention group. For members of the control group the intervention program will not be implemented; At the end of the study, the content of the sexual competence promotion program will be presented. To evaluate the improvement of sexual competence, the researcher-made questionnaire of sexual competence of young adult women, whose validity and reliability will be determined before the start of the study, will be used in two intervention and control groups before, immediately, and 4 months after the intervention.

### Data analysis

Statistical analysis will be done at two descriptive and inferential levels. At the descriptive level, the mean and standard deviation indicators will be used, and at the inferential level, the Variance analysis model with 2 × 3 repeated measures will be used. Statistical analysis is done using SPSS statistical software version 22 and, in all tests, a maximum error of 5% is accepted.

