### Phase II: quantitative study

The aim of the quantitative study is to determine the impact of the intervention program on the sexual competence of young adult women about to get married. This study is a semi-experimental two-group and three-stage study (before, immediately and, 4 months after the intervention) that will be implemented in premarital counseling centers and selected health centers in Isfahan.

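### The 2 × 3 repeated-measures ANOVA treats the baseline score as an outcome, and none of its standard tests isolates the programme's effect at a given follow-up

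*Protocol article*

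**What the plan says.** The Data analysis section of the protocol article states the whole inferential plan for the quantitative phase in one sentence: "the Variance analysis model with 2 × 3 repeated measures will be used". It adds that "in all tests, a maximum error of 5% is accepted". The Phase II section describes a "three-stage study (before, immediately and, 4 months after the intervention"), and the Methods section gives the same three occasions for the competence questionnaire. With two groups, the factor with three levels can only be time with the pre-intervention score included. The Data collection method section of Phase II says that consenting women are allocated to the two groups by randomisation, although the article also calls the design semi-experimental.

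The stated aim of Phase II is the programme's impact on sexual competence, with no time attached. The article does not say whether the group effect, the interaction or a contrast at one follow-up decides that question.

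**The concern.** Under randomisation the arms have equal expected scores before the intervention. Baseline therefore carries no treatment effect, and its best use is as a covariate that removes between-woman variation. As a response level it does harm in three places:

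- **Group main effect.** It averages a true zero at baseline with the effects at the two follow-ups.
- **Group-by-time interaction.** It tests whether the three between-arm differences are equal. It does not show at which follow-up they differ, or whether an early gain survives.
- **4-month contrast within the model.** It is a difference in change from baseline, which is less precise than a baseline-adjusted comparison.

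The conclusion on effectiveness is at stake. The design pays for a 4-month visit, yet a significant interaction would look the same whether or not the benefit was still present then.

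**Working it through.** **Inputs from the article.** The Sample size section gives "α = 0.05, β = 0.1, SD1 = 8.5, and SD2 = 19.8", "37 people in each group", then "110 people (55 people in the intervention group and 55 people in the control group") after "considering at least 20% dropout". Completers per arm at 20% loss: 55 × 0.8 = 44.

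**The plan's own figure.** No target difference is stated, so 37 per group cannot be reproduced, only inverted. Two-sided 5% is assumed.

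- Root mean square SD = √[(8.5² + 19.8²)/2] = 15.24.
- From n = (1.96 + 1.2816)² (8.5² + 19.8²)/δ² with n = 37, δ = 11.48 points, which is 11.48/15.24 = 0.75 SD.

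**Assumptions, because the article does not give them.** Equal SDs, compound symmetry with between-visit correlation ρ of 0.3 to 0.8, and an effect d (in SD units) of 0.5 or the back-solved 0.75. In the formulas n = 44 per arm. Power comes from the noncentral F distribution with noncentrality λ.

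**1. Group main effect.** For between-arm differences (0, d, d) the average is 2d/3. The variance of a woman's three-visit mean is (1 + 2ρ)/3, so λ = (n/2)(2d/3)² × 3/(1 + 2ρ), on 1 and 86 df. At d = 0.5 and ρ = 0.5, λ = 22 × 0.1111 × 3/2 = 3.67 and power is 47%.

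**2. Interaction.** λ = (n/2) Σ(d_t − d̄)²/(1 − ρ), on 2 and 172 df. For a transient gain (0, d, 0), Σ(d_t − d̄)² = 2d²/3. For a sustained gain (0, d, d) it is also 2d²/3. The rejection probability is therefore identical. At d = 0.5, λ = 22 × 0.1667/(1 − ρ) = 5.24, 7.33 and 12.22 at ρ = 0.3, 0.5 and 0.7.

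**3. Effect at 4 months.** The change contrast has variance proportional to 2(1 − ρ), and ANCOVA to 1 − ρ². The ratio is 2/(1 + ρ) = 1.54, 1.33, 1.18 and 1.11 at ρ = 0.3, 0.5, 0.7 and 0.8. At d = 0.5 and ρ = 0.5, λ = 5.5/(2 × 0.5) = 5.50 for change and 5.5/0.75 = 7.33 for ANCOVA.

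| d | ρ | Interaction, transient or sustained gain | Group effect, sustained gain | 4-month change contrast | 4-month ANCOVA |
|---|---|---|---|---|---|
| 0.5 | 0.3 | 51.6% | 56.2% | 50.0% | 68.1% |
| 0.5 | 0.5 | 66.9% | 47.4% | 64.0% | 76.3% |
| 0.5 | 0.7 | 88.3% | 40.9% | 84.9% | 90.1% |
| 0.5 | 0.8 | 97.5% | 38.3% | 95.6% | 97.2% |
| 0.75 | 0.3 | 87.4% | 89.1% | 84.0% | 95.6% |
| 0.75 | 0.5 | 96.1% | 81.4% | 93.8% | 98.1% |
| 0.75 | 0.7 | 99.8% | 74.1% | 99.5% | 99.8% |

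A simulation of 4,000 runs, with SDs of 8.5 and 19.8 in the two groups and the 0.75 SD effect, agreed with the formulas at ρ = 0.3 to 0.7. In it the 4-month ANCOVA rejected in about 5% of trials when the gain was purely transient, as it should.

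**The case against.** The strongest reply is that repeated-measures ANOVA is a valid and familiar analysis of a pre, post and follow-up design. On this view a condensed article may leave contrasts, covariates and multiplicity rules to an analysis plan that is not shown. That stands for silence on detail. It does not cover the model that the article does fix, in which baseline is a response.

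The efficiency argument also has limits. Neither ρ nor the effect size is given. At 0.75 SD the 4-month change contrast loses 11.6, 4.3 and 0.3 percentage points to ANCOVA at ρ = 0.3, 0.5 and 0.7. At 0.5 SD and ρ = 0.8 the interaction matches ANCOVA for a sustained effect (97.5% against 97.2%). The loss is real at low to moderate correlation, but it is not universal.

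Three stronger readings are tempting and are not supported:

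- **Inflated false-positive rate.** A reader might infer two separate follow-up tests at 5% each. The article plans no such tests; it names the ANOVA and a 5% limit. If contrasts were run only after a significant interaction, simulation under the global null gives 4.3% to 4.5% for any false positive.
- **Success claimed on knowledge that fades.** The outcome is a researcher-made competence questionnaire, and its content cannot be seen. The article also does not say that a significant interaction will be reported as lasting benefit.
- **Four months as the only legitimate target.** The aim names no time, and the abstract speaks of competence just before marriage. An immediate effect could be a proper target.

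**Conclusion.** The concern holds as a choice of model that should be changed. With baseline as an outcome level, the group main effect understates a sustained effect by one third. The interaction cannot separate a vanished gain from a lasting one, and this second result does not depend on the effect size or on ρ: under compound symmetry the two noncentralities are equal. The percentages do depend on the assumed effect, the assumed ρ and 44 completers per arm.

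The precision loss at 4 months is the weaker part. At 0.5 SD it is 18, 12 and 5 percentage points at ρ = 0.3, 0.5 and 0.7, and it is negligible at about 0.75 SD with ρ of 0.7 or more. The finding does not show that the ANOVA is invalid, that the error rate exceeds 5%, or that the sponsor intends to claim durability from the interaction.

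**What to change.** Replace the 2 × 3 ANOVA with a mixed model in which the immediate and 4-month scores are the responses. Include baseline score as covariate, arm, visit and arm-by-visit, with unstructured covariance. Report the baseline-adjusted between-arm difference with 95% CI at each follow-up.

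Name one of the two differences as the primary test at two-sided 5%, and treat the other as secondary. Four months is the natural choice if a lasting effect is the aim. The documents name no time, so the sponsor must choose, and should do so before data are analysed. State that neither the group main effect nor the omnibus interaction alone will support the claim of effectiveness.

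The cost is a change of wording and of SPSS syntax, with no added participants or visits. The one trade-off is that an effect seen only at the non-primary time no longer counts as primary success.

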### Ethical considerations

This study has been approved by the Ethical Committee of Isfahan University of Medical Sciences. (IR.MUI.NUREMA.REC.1402.160). The researcher will obtain informed consent from the participants for each step of the research. If the participants do not want to continue the study, they can withdraw from the study. In the literature review phase, the principles of literary rights will be observed and the most accurate translation of the contents into Farsi will be done along with citing the sources.

## Discussion

Preparing young people to start safe and satisfactory sexual behaviors and as a result to acquire sexual competence can play an important role in ensuring their sexual health. Lack of sexual competence is associated with negative consequences, including increased risk of sexual assault and sexual victimization, negative emotions (such as anger, sadness, fear, and humiliation), increased likelihood of high-risk sexual behaviors (such as not using condoms in sexual relations, drug use) and alcohol before sex, non-use of contraceptive methods) and decreased sexual satisfaction [31]. Therefore, the first step to reduce these side effects is sexual education. According to the published report on the state of comprehensive sexuality education (CSE) in 2021, in 15% of the 155 countries surveyed, there is no policy or law related to sexuality education [32]; As a result, girls without sexual competence face more bad consequences in this field. Because in many societies talking about sexual issues under the age of 18 faces many political, legal, cultural, and religious obstacles; time of marriage can be a good opportunity to receive this training and acquire sexual competence among young people who have been deprived of receiving scientific, up-to-date, accurate and complete training. Therefore, adulthood (18–25 years old) is a good opportunity to learn about reproductive and sexual rights and education and to establish the foundations of sexual health. In the current study, the nature of the research questions is such that first, the status of sexual competence of young adults about to get married should be explained with a qualitative method, then based on the findings and after reviewing the literature, a plan to improve sexual competence should be developed. and its effectiveness will be determined by conducting a quantitative study. Therefore, the best methodology to answer the question of this research is a combined method with a sequential exploratory approach. The sequential exploratory approach is a well-known method of conducting research, especially when little information is available on the topic under study. It is also a good way to get participants’ experiences. Actually, when a research method is not enough to reveal the subject of study, it is better to use a combination of both quantitative and qualitative methods [33].

In most of the research conducted on adolescents and young people, other aspects of sexual life such as sexual experiences [34], sexual adaptation [35], and sexual violence [36] have been addressed; As a result, research on the needs of women’s sexual competence at the time of marriage and ways to improve it can be an effective step in developing and improving the content of sex education before marriage. The results of this study can be used by teachers of pre-marriage classes, midwives, gynecologists, reproductive health specialists, psychiatrists, and psychologists who work in the field of sexual health.

## Data Availability

The datasets used and/or analyzed during the current study are available from the corresponding author on reasonable request.
